**3. Caregiver recruitment**

We also wish to gather the views of the informal caregiver. The identifying clinician or the researcher will give written information to the person that the patient identifies as nearest to him or her (such as a family member or informal carer if present) about the study. If the informal carer is interested and meets the inclusion criteria they can be approached and consented (following the minimum of 24 hours unless they decide to waive this period). They may consent at the same time as the patient consents, or separately. The caregiver will complete the questionnaire themselves and return to the researcher at the visit or post it back in a prepaid envelope. Other alternatives, e.g. face-to-face assistance can be discussed. There will be a slightly extended questionnaire for the caregiver to complete if the patient lacks capacity from the start of the study so that we are able to capture some demographic details about the patient too.

**16.3.2 The Mental Capacity Act 2005**

We apply the principles of the Mental Capacity Act (MCA) 2005. We include patients who might lack capacity to consent themselves, as cognitive impairment is not uncommon in individuals at advanced stages in the disease trajectory. The feasibility components of our phase II trial indicated that exclusion of those with cognitive impairment excluded those with the highest disease burden, who are likely to benefit most from the intervention. Exclusion hampers the generalisability of the study for the population it seeks to benefit. We apply the principles of the Act, in other words the work is justifiable because the patients stand a chance of benefiting from inclusion, the research is likely to benefit people like those included in the study, and we cannot obtain information about the effects of SIPC on patients who are most severely affected and lack capacity, without including such patients in the study. Assent is sought from personal consultees (usually close caregivers/family members) who know the patient sufficiently well to give an opinion as to whether or not the individual would have wanted to participate. This approach was tested in the phase II trial, proved successful and was strongly supported by the MS Society and other patient groups. Data are collected from both patients and caregivers, so where patients have low levels of cognitive impairment, we are able to analyse the secondary outcomes, and caregivers assessment of the patient outcomes (separately from patients' self assessments). Incapacitous patients who show distress (verbally or non-verbally) apparently as a result of participation, or voice any objection to the study can be withdrawn at any stage and that withdrawal will not affect their usual care.

### *16.3.3 Process of consent and assent for adults lacking capacity*

The process of consent and assent for adults lacking capacity is shown in Figure 2. The commonality of cognitive impairment in advanced and end of life care requires the inclusion of people with impaired mental capacity in the study. The MCA informs the process of consent protocol and recent studies involving adults lacking capacity [47-49]. All participants are considered to have capacity unless established otherwise and all practicable steps are taken to enable individuals to decide for themselves if they wish to participate. A potential participant's level of capacity is discussed with the referring clinician to identify participants with possible impaired capacity and to anticipate the likely consent procedure. Capacity is established when meeting the individual using the MCA four step process: 1) the individual is able to understand the information about the study; 2) retain the information (even for a short time); 3) use or weigh up that information and 4) communicate their decision [50]. Potential participants' mental capacity is anticipated as ranging from able to give informed consent to lacking capacity to give informed consent. We have developed processes of consent and assent that are tailored to an individual's level of capacity, incorporating varying levels of capacity and anticipating that some participants may lose capacity during the study because. Incorporating different processes of consent and assent is used in research studies on end of life care [47-49]. This intends to enable individuals with varying levels of capacity to decide for themselves if they wish to participate, and to incorporate a process of assent for adults lacking capacity.

### *16.3.4 Consent in the moment for participants with impaired capacity*

For adults with impaired capacity, who are able to understand, retain and weigh-up information in the moment, a process of consent in the moment is used with ongoing consent whereby informed consent to participate is reaffirmed prior to each data collection point [6]. The approach of consent in the moment was developed and used in studies involving adults with dementia and/or cognitive impairment [6 51]. If a participant's capacity declines so that they are no longer able to give informed consent in the moment, the researchers follow the procedure for adults lacking capacity detailed below.

### *16.3.5 Advance consent and assent for participants who lose capacity*

An advance consent is incorporated in anticipation that some participants may lose capacity and may no longer have capacity to indicate their right to withdraw from the study. The process of advance consent is informed by previous studies with older people [47] and on end of life care [52]. Participants able to give informed consent are asked to indicate should they lose capacity in the future if they would wish to continue to be involved in the study, and if yes, then they are asked to nominate a personal consultee (e.g. next of kin). The personal consultee is approached if the participant loses capacity to such an extent that they are no longer able to indicate their right to withdraw from the study, or to complete patient reported outcome measures, requiring instead a proxy informant (e.g. informal or formal carer). The procedure of assent for adults lacking capacity is followed to ascertain the personal consultee's opinion on the individual's continued participation (see below). There will be instances in which a patient's capacity has to be enhanced, e.g. by providing only essential information about the project, breaking down complicated information into smaller points [53]. We already aim to make the information sheet easily accessible and to give patients time to reach their decision and pose questions. If patients' capacity can be enhanced they will be able to consent. If not, a personal consultee will be sought.

### *16.3.6 Assent for adults lacking capacity*

When an adult lacks capacity a personal consultee is sought to give an opinion as to whether in his/her knowledge of the potential participant they would have wanted to participate in the study had they had capacity to indicate this, and that participation would not cause undue distress [47 50]. A personal consultee comprises next of kin, immediate carer or attorney with Lasting Power of Attorney. Identified consultees are given an information leaflet about the study, a letter detailing why they have been chosen as a consultee and their responsibilities as a consultee. The consultee documents are informed by research with elderly people [47], the MCA [50] and MCA guidance [54].

### *16.3.7 Documentation of study participation*

All participants who give written consent to participate will be given a copy of the information sheet to retain and keep, and all consultees giving written assent. Participants are offered a copy of their signed consent form to keep if they wish, and consultees a copy of their signed assent form. A copy of the signed consent/assent form will be filed in the participant's medical notes. The research team will retain the original

signed consent form. For those people who give consent /assent for their general practitioner (GP) to be informed about their participation in the study (on the consent form), the GP will be sent a letter.

**Figure 2: Process of consent for mental capacity**

[figure not shown]

### 16.4 Randomisation Procedure / Code Break

Following consent, baseline interview and registration of patient on the MACRO eCRF, the patient will be allocated a unique PIN which will identify them throughout the course of the trial. The individuals will be randomised to one of the trial arms using minimisation method, stratified by center, primary diagnosis (MS, IPD, PSP & MSA, and MND) and cognitive impairment. Randomisation will be done in a 1:1 ratio and will be at the patient level. Randomisation will be performed using an online randomisation system based at King's Clinical Trials Unit (King's CTU), which can be accessed at [www.ctu.co.uk](http://www.ctu.co.uk) by clicking 'randomisation – advanced' on the lower right hand side of the page. The trial coordinator (or someone supervised by the TM) will be notified of the trial arm allocation of the patients and arrange intervention and/or follow-up visits. The research nurses who will conduct the interviews and the trial statistician will be blinded to the trial arm allocation. Overall, we do not expect to need to unblind (code break) to the research nurses or to the trial statistician during the periods of trial and primary analysis. After the primary endpoint of 12 weeks, in a small number of cases research nurses are needed to conduct a qualitative interview with a patient who has received the intervention, where we cannot find another researcher to do this interview, which will effectively unblind the research nurses. We will keep this to a minimum and ensure it is after the primary endpoint of the study.

Any problems with the online randomisation system should be reported to the Trial Manager or the King's CTU at [[contact]](mailto:[contact]) or on [name].

## **16.5 Withdrawal of Subjects**

Patients can withdraw from the study at any time for any reasons without affecting their usual care. Should a patient decide to withdraw from the study, all efforts ethically appropriate will be made to report the reason for withdrawal as thoroughly as possible. Should a patient withdraw from receiving intervention only, efforts will be made to continue to obtain follow-up data, with the permission of the patient or family as appropriate.

## **16.6 Expected Duration of Trial**

The trial will run for 40 months, which includes trial set up, recruitment and analysis of data. Patients will receive their intervention for approximately 6-8 weeks and will be followed up for 24-26 weeks (from start of trial, not necessary start of intervention). End of trial is defined as the last patient's last study visit.

# **17. Trial Procedures and Data Collection**

## **17.1 Main data collection by visit**

Following referral, the key worker (usually a specialist palliative care nurse) from the MPCT contacts the patient within 2 working days to arrange a visit within the next five working days to undertake a comprehensive palliative care assessment. In keeping with the multi-disciplinary ethos of palliative care, the detailed assessment is discussed with the MPCT who suggest ways to improve management of physical, emotional, social and other problems, provide specialist welfare benefits advice, liaises with and acts as a catalyst with local health services, both primary and specialist teams, and social care (See Figures 1 and 3). There are two follow-up visits to action, review and evaluate the proposed plan of care, and then discharge to local services as appropriate. The key worker liaises regularly and integrates care with neurologists, nurses, and rehabilitation, primary and hospice services to discuss patients of concern. The key worker records the nature of assessments and services provided.

## **17.2 Research interviews**

Interviewers undertake face-to-face interviews with patients (at the patient's location of choice (e.g. home or at a clinic)) and assist as required in self completion of caregiver questionnaires. These are conducted according to a standardised schedule, using trained experienced interviewers who follow a manual for researchers, who are blind to treatment allocation and accommodated separately from the intervention team. Assessments from the nearest caregiver, family member or friend are planned to coincide with the patient assessments (ie at baseline, 6,12,18,24 weeks post randomisation). Usually they will self-complete the follow up questionnaires and return these by post to the project team at King's College London. If this is not possible telephone assistance or face-to-face interview will be offered. In some instances caregivers may need a visit, or will choose to self-complete the questionnaire during the patient interview. We have used this method successfully in studies with people with MS and PRDs. For adults lacking capacity baseline and outcome measures are obtained from the informal caregiver interviewer as above. The use of a proxy informant is common in research on palliative care associated with patients' advancing illness and deteriorating condition, and the importance of capturing data at points of deterioration when a patient may most benefit from palliative care, notably the last days of life [55]. Research on proxy informants indicates higher agreement between patient and caregiver dyads than in patient and health care provider dyads [56]. In addition the informal caregiver provides the baseline information about the patients demographic circumstances and clinical history (e.g. age, educational level, diagnosis, time since diagnosis) as would normally be collected in the patient interview.

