| Endpoints:                       | 
Primary endpoint
 
A combined score of eight key symptoms, measured by symptom subscale of the Integrated Palliative care Outcome Scale for neurological conditions (IPOS Neuro-S8) at 12 weeks post randomisation (primary objective)
 
Secondary endpoints
 
 
1. Patients' other symptoms and palliative care needs: measured by the relevant symptom component of the IPOS Neuro
 
2. Patients' health-related quality of life and well-being: measured by the EQ-5D and ICECAP-A
 
3. Patients' psychological distress: measured by the 14 item Hospital Anxiety and Depression Scale (HADS), patient reported
 
4. Patients' satisfaction, self-efficacy and other aspects: measured by the modified FAMCARE scale (FAMCARE-P16), the Self-Efficacy to Manage Chronic Disease Scale (SEMCD), an advance care planning scale and some questions covering patients' experiences of the study
 
5. Hospital admissions, length of hospital stay, emergency attendance and other service use during the course of the study: measured by an adapted version of the Client Service Receipt Inventory (CSRI), and survival from consent (days)
 
6. Caregiver burden, positivity and quality of life: measured by the Zarit Burden Inventory (ZBI-12) (12 item version+8 positive items), the VR-12 and the modified FAMCARE scale (FAMCARE 2), as self-assessed by caregiver
 
7. Caregiver assessment of patients' outcomes: using the same measures (IPOS Neuro and CSRI) and used to aid imputation of missing patient data)
 
8. Observer (completed by the researcher) assessment of the patients' problems: measured by the Support Team Assessment Schedule (STAS)
 
 
The main endpoint is at 12 weeks before the standard care arm receiving the intervention.
 |

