**Figure 3: Summary schedule of study**

| Timeline                                                                  | Fast track (immediate referral to palliative care service) | Standard care (waiting list control) |
|---------------------------------------------------------------------------|------------------------------------------------------------|--------------------------------------|
| Consent and Baseline interview                                            | a                                                   | a                             |
| Randomisation                                                             |                                                            |                                      |
| 2 working days from receiving information about patient                   | b                                                   |                                      |
| 1-6 weeks                                                                 | c                                                   |                                      |
| 6 weeks                                                                   | d                                                   | d                             |
| 6-8 weeks                                                                 | e                                                   |                                      |
| 12 weeks                                                                  | f                                                   | f                             |
| 2 working days after receiving research nurse data from week 12 interview |                                                            | g                             |
| 12-18 weeks                                                               | h                                                   | i                             |
| 18 weeks                                                                  | j                                                   | j                             |
| 18-20 weeks                                                               |                                                            | k                             |

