| 24 weeks                                                                  | l                                                   | l                             |
| 24-26 weeks                                                               |                                                            | h                             |

|          |                                                                                                                             |
|----------|-----------------------------------------------------------------------------------------------------------------------------|
| a | Baseline research interview and consent on entry to the study before randomisation                                          |
| b | Palliative care assessment within 2 working days                                                                            |
| c | Palliative care team care, including assessment, treatment, referral                                                        |
| d | Research interview at 6 weeks after randomisation                                                                           |
| e | Palliative care team care continues usually ending by 6-8 weeks, with referral on for those patients needing long-term care |

|          |                                                                                                                                                |
|----------|------------------------------------------------------------------------------------------------------------------------------------------------|
| f | Research interview at 12 weeks after randomisation                                                                                             |
| g | Standard care group now offered palliative care team who see person within 2 working days of receiving information                             |
| h | Patients now discharged from palliative care team, if have been referred on some under care of community team, which continues from this point |
| i | Palliative care team now providing care in standard care group, following their 12 week wait                                                   |
| j | Research interview at 18 weeks                                                                                                                 |

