## 20. Statistics

### 20.1 Sample Size

Based on the data from our Phase II MS trial, the five centres altogether need to recruit 356 patients. In view of the advanced illness in this patient group we have allowed 20% attrition (phase II trial attrition from death or illness: 3/52) to the primary 12-week outcome, giving 296 patients, or 148 in each arm with both baseline and 12-week outcome data. The correlation between baseline and the 12-week outcome in the pilot study was 0.55. Using generalised linear model to adjust for the baseline score, with two-sided  $\alpha=0.05$  and correlation of 0.40, the study will have 80% power for a medium effect size of 0.30. To allow for heterogeneity across conditions and centres, we used conservative figures (eg. correlation 0.4 rather than 0.55; 20% attrition) to estimate the sample size. For the qualitative study, we estimate a sample size in each study site of seven patients/caregivers, total 35 patients/ caregivers in qualitative sample and six service providers/service commissioners from each site, total of 30 providers/commissioners. For the pilot phase we aim to recruit 15-25 patients/caregivers. The survey of health professionals will be primarily descriptive. It will be sent to a random sample of 200 health professionals, 40 in each area, with a mix of primary and secondary care staff identified as those referring to or interacting with SIPC. We estimate a response rate of 50-60% with 2 reminders giving at least 100 completed questionnaires.

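### Control caregivers' week-12 forms can be completed after SIPC has begun, because the cross-over waits only for the patient interview while caregiver forms usually come by post

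*Protocol*

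**What the plan says.** **Caregiver data.** Section 17.2 intends caregiver assessments to fall at the same time as the patient's, at baseline and weeks 6, 12, 18 and 24. On how they are returned it says: "Usually they will self-complete the follow up questionnaires and return these by post to the project team". Telephone help, a face-to-face interview, or completion during the patient's interview are also allowed, and section 16.3.1 (caregiver recruitment) lets the form be handed to the researcher at the visit. No window, latest completion date or rule for late forms is given.

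**Control-arm cross-over.** The synopsis (comparator) offers SIPC to controls once the second follow-up interview has been finished and looked over. Figure 3 places this step at "2 working days after receiving research nurse data from week 12 interview", and its key adds: "Standard care group now offered palliative care team who see person within 2 working days of receiving information". Sections 14.2 and 17.1 instead give a call within 2 working days and a visit within the following 5. None of these places mentions the caregiver form.

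**Principle.** The synopsis states: "The main endpoint is at 12 weeks before the standard care arm receiving the intervention".

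**The concern.** The 12-week contrast means SIPC against no SIPC only if both arms are measured before controls are exposed. For patients the order is secured, because the interview itself starts the clock. For caregivers it is not: the clock runs on another person's data, and the caregiver's own form may still be on the kitchen table.

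SIPC reaches caregivers early. The intervention manual (section 3) has the first call cover the family's concerns where appropriate, and visit 1 includes an assessment of the caregiver and an agreed action plan. The outcomes exposed are the ZBI-12 with positivity items, VR-12, FAMCARE 2, and the carer versions of IPOS Neuro and CSRI. Caregiver burden and quality of life are part of a stated secondary objective, and section 20.2.1 analyses the ZBI-12 in the same way as the primary outcome.

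The error runs one way. Lateness in the fast-track arm does not move anyone between conditions; lateness in the control arm can. If SIPC truly helps caregivers, the expected distortion is towards no effect.

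**Working it through.** **1. Gap between the patient's interview and SIPC contact in the control arm**

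- Shortest: nurse data arrive the same day and Figure 3 applies, giving about 2 working days.
- Sections 14.2 and 17.1, same-day data: call by 2 working days, visit by 2 + 5 = 7 working days.
- Slow data: section 26.1 aims for eCRF entry within 7 days. Assuming the data reach the coordinating team only then, a visit comes by 7 days plus 7 working days (9 to 11 calendar days), that is 16 to 18 days, or about 2.5 weeks.

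Figure 3 (seen within 2 working days) and sections 14.2 and 17.1 (called within 2, visited within a further 5) do not agree and should be reconciled. The gap in the caregiver sequence exists under either.

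**2. The plan's own power figure**

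No power statement is made for caregivers, so the primary-outcome figures are borrowed as a yardstick. Section 20.1 states "correlation of 0.40, the study will have 80% power for a medium effect size of 0.30", with attrition "giving 296 patients, or 148 in each arm with both baseline and 12-week outcome data".

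- Baseline-adjusted SD = √(1 − 0.40²) = √0.84 = 0.917
- n per arm = 2 × (1.96 + 0.842)² × 0.84 / 0.30² = 147, against the plan's 148
- Power at 148 per arm = Φ(0.30 × √(148/2) / 0.917 − 1.96) = 80.4%

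The stated figure is reproduced. Using 148 caregivers per arm is generous, since not every patient need have a participating caregiver.

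**3. Attenuation**

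Let q be the share of control caregivers who complete the form after SIPC contact, and f the share of the full effect already present when they do. The control mean moves by q × f × d, so the expected difference is d × (1 − q × f). The documents give neither q nor f, so every row below is an assumption.

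| q | f | Loss q × f | d | Power, 148 per arm |
|---|---|---|---|---|
| 0 | any | 0% | 0.300 | 80.4% |
| 10% | 10% | 1% | 0.297 | 79.6% |
| 10% | 25% | 2.5% | 0.2925 | 78.4% |
| 20% | 50% | 10% | 0.270 | 71.7% |
| 30% | 50% | 15% | 0.255 | 66.8% |

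With an assumed 104 caregivers per arm (70% of 148), power is 65.4% without late forms, 63.2% at 10%/25% and 51.7% at 30%/50%.

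**The case against.** **Posting is not lateness.** A form completed on schedule and posted is valid however long the post takes. The assessments are meant to coincide with the patient's, and interviewers help with completion when asked. This stands: the documents show that late completion is possible, not that it happens.

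**The gap can be longer than it first looks.** If nurse data take a week to arrive, a form one week late may still precede any contact. This also stands. A reader might infer from Figure 3 that any form a few days late is contaminated; that is only the shortest case.

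**Early contact may change little.** SIPC is usually three visits over 6 to 8 weeks. A reader might assume q and f of 50% or more and infer that a quarter or half of the caregiver effect is lost. Nothing in the documents supports so much effect after a call or one visit, and the low end of the range (1% to 2.5%) is at least as credible.

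**The primary outcome.** A reader might infer that the synopsis sentence on the main endpoint is broken. It is not: the patient-reported IPOS Neuro-S8 is collected at the interview that triggers the cross-over. A reader might also extend the point to patients lacking capacity, whose outcomes come from the caregiver. The sentence on this in section 17.2 is unclear and may mean an interview rather than a posted form, so the extension is not established. The synopsis does say carer ratings may aid imputation of missing patient data, but gives no detail from which to judge any effect on the primary result.

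**Late forms can be handled in the analysis plan.** Partly true. The SAP can set the rule, but it cannot recover the order of events unless the caregiver's completion date was collected, and order of collection is a matter for the protocol.

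**Conclusion.** The point holds in a limited form. Control-arm SIPC is tied to the patient's interview, caregiver forms are posted by default, and no provision keeps the second ahead of the first. Control caregiver outcomes at week 12 can therefore be measured after exposure, in that arm only. If SIPC benefits caregivers, the estimate could be biased towards zero.

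The size cannot be derived from the documents. Under the assumptions shown it runs from about 1% of the difference to 15%, and it may well sit near the lower end. This is a cheap improvement that protects a stated secondary endpoint; it does not threaten the primary result.

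**What to change.** In section 17.2, for week 12 only and in both arms:

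- Send the caregiver form ahead of the patient's week-12 interview and make completion at or before that interview the default. It is handed to the nurse in a sealed envelope, or completed by telephone the same day. Post remains the fallback. Apart from the earlier mailing and the envelope, section 17.2 already permits these routes.
- Record the date the caregiver completed the form. The palliative care team already logs the date of first telephone contact (manual, section 3 and Appendix 2), so the two can be compared. Because contact dates reveal allocation, keep that comparison away from the blinded statistician until the primary analysis is done.
- Keep all forms in the main caregiver analysis as randomised. Add a sensitivity analysis that applies the same cut-off, counted in days from the patient's interview, to both arms. Setting only late control forms to missing would create missingness that differs by arm through a post-randomisation event, and should be avoided.

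Cost: slightly longer week-12 visits for some pairs, an earlier mailing and one date field. The timing of the SIPC offer to controls does not change.
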